## Abstract

**Background:**

Antipsychotic drugs are primarily efficacious in treating positive symptoms by blocking the dopamine D2 receptor, but they fail to substantially improve negative symptoms and cognitive deficits. The limited efficacy may be attributed to the fact that the pathophysiology of psychosis involves multiple neurotransmitter systems. In patients with chronic schizophrenia, memantine, a non-competitive glutamatergic NMDA receptor antagonist, shows promise for ameliorating negative symptoms and improving cognition. Yet, it is unknown how memantine modulates glutamate levels, and memantine has not been investigated in patients with first-episode psychosis.

**Aims:**

This investigator-initiated double-blinded randomized controlled trial is designed to (1) test the clinical effects on negative symptoms of add-on memantine to antipsychotic medication, and (2) neurobiologically characterize the responders to add-on memantine.

**Materials and Equipment:**

Antipsychotic-naïve patients with first-episode psychosis will be randomized to 12 weeks treatment with [amisulpride + memantine] or [amisulpride + placebo]. We aim for a minimum of 18 patients in each treatment arm to complete the trial. Brain mapping will be performed before and after 12 weeks focusing on glutamate and neuromelanin in predefined regions. Regional glutamate levels will be probed with proton magnetic resonance spectroscopy (MRS), while neuromelanin signal will be mapped with neuromelanin-sensitive magnetic resonance imaging (MRI). We will also perform structural and diffusion weighted, whole-brain MRI. MRS and MRI will be performed at an ultra-high field strength (7 Tesla). Alongside, participants undergo clinical and neuropsychological assessments. Twenty matched healthy controls will undergo similar baseline- and 12-week examinations, but without receiving treatment.

**Outcome Measures:**

The primary endpoint is negative symptom severity. Secondary outcomes comprise: (i) clinical endpoints related to cognition, psychotic symptoms, side effects, and (ii) neurobiological endpoints related to regional glutamate- and neuromelanin levels, and structural brain changes.

**Anticipated Results:**

We hypothesize that add-on memantine to amisulpride will be superior to amisulpride monotherapy in reducing negative symptoms, and that this effect will correlate with thalamic glutamate levels. Moreover, we anticipate that add-on memantine will restore regional white matter integrity and improve cognitive functioning.

**Perspectives:**

By combining two licensed, off-patent drugs, AMEND aims to optimize treatment of psychosis while investigating the memantine response. Alongside, AMEND will provide neurobiological insights to effects of dual receptor modulation, which may enable future stratification of patients with first-episode psychosis before initial antipsychotic treatment.

**Clinical Trial Registration:**

[ClinicalTrials.gov], identifier [NCT04789915].

## Introduction

Antipsychotic medication (AP) is primarily effective in treating positive psychotic symptoms such as delusions, hallucinations, and disorganized thinking, which are cardinal symptoms of schizophrenia. However, AP does not ameliorate the accompanying negative symptoms (e.g., anhedonia, avolition, and social withdrawal), and cognitive deficits, which are highly disabling and predictive of patients’ long-term prognosis (1–3). Persistent negative symptoms have also shown to be a critical predictor for future treatment resistance (4). A growing body of evidence support that a shortening of the interval between onset of psychosis and initiation of an efficient intervention lead to better long-term outcome (5–7).

The pathophysiology of psychosis is complex and involves multiple neurotransmitters, e.g., serotoninergic- (8), GABAergic, and glutamatergic (9) systems. Nevertheless, modulation (particularly antagonism) of striatal dopamine D2 receptors (D2R) remain the key common denominator of all licensed antipsychotics (10). Even so, around 30% of patients with psychosis display inadequate response to antidopaminergic treatment (11, 12). Mounting evidence from post- mortem-, brain imaging-, genetic-, and pharmacologic challenge studies indicate glutamatergic dysregulation, specifically of the N-methyl-D-aspartate receptor (NMDAR), as part of the pathophysiology of psychosis and schizophrenia (13–15). Through excitotoxicity, glutamate dysregulation may underlie structural degeneration, e.g., in hippocampus, which is a key finding in patients with schizophrenia (16–19).

Using 3T magnetic resonance spectroscopy (MRS), we recently reported increased thalamic glutamate levels in antipsychotic-naïve patients with first episode psychosis (FEP) compared to healthy controls (HC). Importantly, high thalamic glutamate levels predicted poor treatment response (9). Other studies have also associated glutamate levels with treatment outcome (20–22). Nevertheless, cross-sectional studies of glutamate levels between patients with FEP and HC have shown inconsistent results, (21, 23, 24) likely reflecting differences in glutamate levels across brain regions and in patients’ variable previous antipsychotic exposure, as well as the complexity of the disorder, with individual differences regarding the neurobiological findings Studies have also shown that thalamic glutamate levels are heritable, genetically related to psychosis (25), and that in individuals at ultra-high risk of psychosis (UHR), thalamic glutamate levels are related to attention and level of functioning (26, 27). Moreover, we previously demonstrated that thalamic and anterior cingulate cortex (ACC) levels of glutamate are associated with symptomology and cognition, specifically spatial working memory, set-shifting and sustained attention both in UHR and FEP (9, 26, 28, 29).

Cutting-edge 7T MRS can non-invasively determine brain metabolite levels of e.g., γ-aminobutyric acid (GABA), N-acetylaspartate, N-acetylaspartyl and importantly, 7T allows for discrimination of glutamate concentrations from glutathione and glutamine (22, 30, 31). Moreover, multiple voxels/brain regions can be investigated with 7T. In the context of glutamate and psychosis, the thalamus, ACC, hippocampus, dorsolateral prefrontal cortex (DLPFC), and basal ganglia are of particular interest, e.g., (17, 29, 32–34).

Regarding brain structure, the use of structural 7T sequences offers increased sensitivity to quantify neurodegenerative processes such as volume loss e.g., by hippocampal subfield segmentation (35).

Also, high-resolution quantification of tissue parameters such as iron deposition using quantitative susceptibility mapping allow characterization of subtle changes in the “dopaminergic regions” of the basal ganglia, including striatum, pallidum, and substantia nigra (SN) (35). Recently, a promising non-invasive method for *in vivo*-investigating dopamine in neuropsychiatric illness has been developed. Neuromelanin-sensitive MRI (NM-MRI) purports to detect the content of neuromelanin (NM), a product of dopamine metabolism that accumulates in the SN. NM may be regarded as a proxy of structural and functional integrity of dopaminergic cells in SN (36). Findings indicate that NM-MRI signals correlate with NM concentration, dopamine levels in the striatum and severity of psychosis in schizophrenia, even without neurodegeneration (37).

NMDA-receptor modulation has been investigated in several preclinical studies (38–40). Interestingly, different NMDA-receptor compounds lead to various effects on molecular, anatomical, and behavioral levels. Specifically, memantine exerts opposite effects than ketamine on the genetic level, which may underlie the two drugs’ different clinical effects (38, 41).

Against this background, modulation of glutamatergic NMDAR has been investigated as a potential treatment target in patients with schizophrenia or other psychotic disorders. Memantine is a non-competitive NMDAR antagonist used for treatment of Alzheimer’s disease. Two recent meta-analyses (42, 43) and one systematic review (44) have concluded that adjunctive memantine to antipsychotics is safe and significantly improves negative symptoms in chronic medicated patients with schizophrenia. One of the meta-analyses also indicated a potential beneficial effect on global levels of cognition of patients treated with adjunctive memantine compared to the placebo group (42).

Memantine has been theorized to ameliorate progression of negative symptoms by counteracting excitotoxicity correlated to high glutamate levels in early stages of psychosis (45), but this has not yet been investigated in initially antipsychotic-naïve patients.

AMEND is an ongoing double-blinded clinical trial (Clinicaltrials.gov, ID: NCT04789915), where antipsychotic-naïve patients with first-episode psychosis will be randomly allocated to treatment with first-line antipsychotic compound with addition of memantine or placebo. Patients will be matched with HCs and all participants will undergo baseline and 12-weeks examinations (Figure 1).

**FIGURE 1 F1:**
[figure not shown]
AMEND flow chart.

We hypothesize that add-on memantine to amisulpride will be superior to amisulpride monotherapy in reducing negative symptoms, and that this effect will correlate with thalamic glutamate levels. Moreover, we anticipate that add-on memantine will restore regional white matter integrity and improve cognitive functioning.

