#### Exploratory Endpoints

Exploratory endpoints include associations between clinical data, quality of life, brain metabolites in other regions, e.g., ACC (33, 34), structural measures (e.g., hippocampus subfields) (35), diffusion data, and basal ganglia quantification (Table 2). Interactions between baseline brain metabolite levels and brain structure and white matter integrity in patients and HC will also be investigated.

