### Planned Statistical Analyses

Homogeneity of variance between the two groups will be assessed using Levene’s test. Parametric data will be evaluated using parametric testing. Non-normally distributed data or data that exhibit unequal variances will be tested using non-parametric tests as appropriate. Fisher’s or χ2 exact tests will be used for group comparisons between categorical data. The Benjamini-Hochberg procedure will be used to control the type I error rate.

Data analyses on the primary outcome and most of the secondary outcomes will be performed before un-blinding and according to the per-protocol principle. Analyses of adverse events will be performed according to the intention-to-treat principle. Demographic variables and clinical characteristics will be reported in frequency for categorical data, and in mean values (with standard deviations and range) for normally distributed, continuous variables. Group comparisons for demographic data will be performed using independent *t*-tests for continuous variables and Chi-square tests for nominal and ordinal variables. Primary and secondary outcomes will be tested using repeated measures (rm)ANOVA.

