### Power Calculation

The power calculation is based on the primary outcome. We used the most representative clinical study we could identify and attempted to modify to the current setting. An 8-week RCT using risperidone plus memantine in stable schizophrenia patients (*N* = 40) reported a reduction in PANSS negative of −2.8 (SD 1.6) with memantine compared to −0.8 (SD 0.9) with placebo (79). Assuming a similar response, we expect add-on memantine to induce −2 ± 2 point more reduction in PANSS negative compared to amisulpride monotherapy. An *a priori* Student *t*-test (two-sided) with significance level α of 0.05 and a desired power (1-α) of 80%, shows that 16 completed patients in each arm is needed.

To increase power of secondary analyses, enrollment will continue until 18 participants in each arm have completed examinations. Moreover, AMEND will be extended to 12 weeks based on the median trial duration in the meta-analysis of add-on memantine [12 weeks (mean 11.5 weeks)] (42). Based on our center’s 20 years of experience with recruitment and treatment of antipsychotic-naïve patients, we expect an inclusion rate of 2 patients per month and an attrition rate of 25%. Thus, recruitment of 46 patients will take approximately 2 years.

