## Discussion

By rational combination of two licensed, off-patent drugs, amisulpride and memantine, AMEND aims to optimize treatment of psychosis, especially the accompanying negative and cognitive symptoms, alongside with unraveling the signature of memantine response. If successful, AMEND will provide pivotal neurobiological evidence for future stratification of patients with first-episode psychosis before initial antipsychotic treatment.

There are few potential risks related to participating in the AMEND study. Side effects of memantine are relatively mild compared to antipsychotic medication. In previous memantine add-on RCTs in schizophrenia patients, the reported side effects did not differ from placebo (42) and chronic patients treated with memantine as add-on treatment had an improvement compared to placebo (79), why we assume that the added treatment also will improve patients with first-episode psychosis. The participants will have the advantages of a thorough examination program with more detailed psychopathological and neuropsychological testing than normally provided.

Magnetic resonance imaging procedures have not been associated with any health risk, however, the examination might cause discomfort for people with claustrophobia and anxiety. Participants will be followed carefully during the project and any potential discomfort will be attempted minimized by research staff. Great care will be taken by the research group to ensure that all examinations are carried out as smoothly and efficiently as possible, including breaks when needed. Scanning will be discontinued in cases of discomfort or anxiety, and communication between staff and participants will be possible during the whole scan.

Participants with head/neck tattoos or permanent make-up might experience warming and soreness of the painted area, and scanning will be interrupted should these symptoms arise. Incidental findings on MRI scans might lead to worrying and further clinical work-up. Blood samplings might cause discomfort for some people but will be taken by trained personal and under hygienic circumstances.

Participants can withdraw from the study at any time without explanation, and without any consequences for the following treatment.

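### Aim 2 and the thalamic glutamate hypothesis concern effect modification, but no stated analysis compares the glutamate–outcome relation between arms

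*Protocol article*

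**What the plan says.** The Abstract (Aims) gives the second purpose of the trial as to "neurobiologically characterize the responders to add-on memantine". The hypothesis at the end of the Introduction, repeated in the Abstract under Anticipated Results, is that add-on memantine will be superior on negative symptoms and that "this effect will correlate with thalamic glutamate levels". It does not say whether baseline glutamate or change in glutamate is meant, gives no direction, and does not say in which patients the correlation is to be computed.

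The Discussion states the intended use: evidence for "future stratification of patients with first-episode psychosis before initial antipsychotic treatment". On the marker itself, the Introduction reports from the group's earlier study of antipsychotic-naïve first-episode patients that "high thalamic glutamate levels predicted poor treatment response".

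Three places bear on the analysis:

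- Secondary Endpoints lists glutamate levels in the five preselected regions, thalamus included, as outcomes.
- Planned Statistical Analyses says "Primary and secondary outcomes will be tested using repeated measures (rm)ANOVA", with no moderator.
- The section Exploratory Endpoints says "Exploratory endpoints include associations between clinical data, quality of life, brain metabolites in other regions". The only interactions it names are these: "Interactions between baseline brain metabolite levels and brain structure and white matter integrity in patients and HC will also be investigated".

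Neither of those interactions involves treatment. Patients in both randomised arms have the baseline and week-12 scans.

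**The concern.** Characterising memantine responders in order to select patients before treatment means asking whether the memantine-minus-placebo difference varies with a baseline marker. In a parallel-group trial no single patient's memantine effect is observed. Improvement in the memantine arm is the sum of response to newly started amisulpride, natural course and any memantine effect. A patient who improves on the combination is therefore not known to be a memantine responder.

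If thalamic glutamate is prognostic under antipsychotic treatment, which the result reported in the Introduction makes plausible, it can correlate with change in either arm whether or not memantine matters. The randomised placebo arm is what could separate the two, and no stated analysis uses it for this purpose. At stake is the second aim and the stratification claim built on it. The primary treatment comparison is not affected.

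**Working it through.** **The plan's own figure.** Power Calculation assumes a difference of 2 points, SD 2, two-sided α 0.05 and 80% power. Then n per arm = 2 × (1.960 + 0.842)² × (2/2)² = 15.7, so 16, as stated. An exact t-test gives 16.7, so 17. At the planned 18 completers per arm, power for the main effect is 83.0%. The size was set for the main effect only.

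**What each test addresses.** Let Y be the reduction in PANSS negative, T = 1 for memantine and 0 for placebo, and G standardised glutamate:

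Y = a + δT + βG + γTG + error.

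The slope on G is β under placebo and β + γ under memantine. The hypothesis and aim 2 concern γ.

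- A correlation in the memantine arm tests β + γ = 0.
- A pooled correlation with 1:1 allocation tests, in effect, the average slope β + γ/2 = 0.
- Only the treatment-by-glutamate term tests γ = 0.

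So with γ = 0 and β ≠ 0 both correlations can be significant with no memantine-specific relation. With β + γ = 0 the memantine-arm correlation is blind to real effect modification, and with γ = −2β the pooled correlation is.

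**Size, by simulation.** Settings: 18 per arm, SD 2, treatment difference 2, two-sided 5%, 10,000 runs, no baseline covariate. The correlations are assumptions, because the article gives none. Entries are the share of trials with p < 0.05.

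| r placebo | r memantine | memantine-arm correlation | pooled correlation | interaction |
|---|---|---|---|---|
| 0.3 | 0.3 | 23% | 35% | 5% |
| 0.5 | 0.5 | 58% | 79% | 5% |
| −0.5 | −0.5 | 59% | 79% | 5% |
| 0 | 0.3 | 23% | 12% | 13% |
| 0 | 0.5 | 58% | 27% | 31% |
| −0.5 | 0 | 5% | 26% | 31% |
| −0.4 | 0.4 | 39% | 6% | 66% |

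The first three rows are a purely prognostic marker. A separate simulation of that case gave 22%, 38%, 59% and 78% for the memantine-arm correlation at r = 0.3, 0.4, 0.5 and 0.6, with the interaction test at 5%.

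**Check by Fisher's z.** Power = Φ(atanh(r) × √(n − 3) − 1.96). For r = 0.5 and n = 18: 0.549 × 3.873 − 1.96 = 0.167, and Φ = 57%. For r = 0.3, 0.4 and 0.6 it gives 22%, 37% and 77%, in line with the simulation.

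**What the interaction can deliver.** For r = 0 versus 0.5, Fisher's z gives Φ(0.549/√(2/15) − 1.96) = Φ(−0.456) = 32%, close to the simulated 31%. For 80% power, n per arm = 2 × (2.802/0.549)² + 3, about 56; for r = 0 versus 0.3 it is about 167. With residual SD 2 and 18 per arm, the slope difference detectable with 80% power is 2.89 × 2 × √(2/17) = 1.98 points per SD of glutamate, as large as the whole assumed treatment effect.

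**The case against.** The strongest reply is that the hypothesis sentence already means the right thing. Its subject is superiority over amisulpride alone, a between-arm contrast, and saying that this contrast varies with glutamate is effect modification in plain words. No within-arm correlation is announced, and a condensed article may leave the model to a fuller document. This stands in part: the simulated rates describe an analysis that the article does not explicitly plan. It does not remove the point. The question is worded through correlation and responders, and the analyses that are named do not match the question under any reading.

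Four further objections limit the claim:

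- The listed exploratory associations refer to metabolites in other regions, so they do not show that the thalamic hypothesis will be tested by simple association. True; equally, nothing else stated tests it.
- Baseline or change in glutamate is left open, and some of the article's language points to mechanism. True; the interaction with baseline glutamate answers only the stratification question.
- The result reported in the Introduction is about treatment response. The article does not tie it to negative symptoms, so a prognostic role for PANSS negative is plausible, not shown.
- High glutamate went with poor response, whereas the excitotoxicity rationale suggests more memantine benefit at high glutamate. A purely prognostic correlation would then have the opposite sign to the rationale, so two-sided significance is not the rate of misreading. This is fair, but the hypothesis states no direction. If memantine offset the poor prognosis (r = −0.5 under placebo, 0 under memantine), the memantine-arm correlation would be significant only 5% of the time and miss it.

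A reader might infer that a spurious memantine predictor would probably be found. The documents do not support that: the rate passes one half only at an assumed r of about 0.5 or more.

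**Conclusion.** The concern holds in limited form. The second aim and the glutamate hypothesis are questions of effect modification, and the stated analyses contain no between-arm comparison of the glutamate–outcome relation. A within-arm or pooled correlation, or a responder grouping, could not supply one if glutamate is prognostic in both arms.

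The 22% to 78% range against 5% illustrates the risk under assumed values of r from 0.3 to 0.6, 18 completers per arm and a purely prognostic marker. It is not a forecast for this trial. The article's statement that the trial is not sized for all exploratory analyses concedes low power, but not that a correlation addresses a different question. This should be put right before analysis, because the stratification claim depends on it.

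**What to change.** State that the hypothesis concerns baseline thalamic glutamate, which is the reading that fits selection before treatment. Test it in all randomised patients with outcome data, using one model: week-12 PANSS negative on baseline PANSS negative, treatment, baseline thalamic glutamate and treatment-by-glutamate. Report the interaction estimate with its confidence interval as an exploratory result. Label within-arm correlations and any responder grouping as descriptive.

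If change in glutamate is meant, say so and treat it as a mediation question, which a correlation does not settle.

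The cost is wording in the analysis plan; no new data are needed. The price is candour about precision. With about 31% power for r = 0 versus 0.5, a non-significant interaction would not rule out effect modification, and the claim about future stratification has to be made more cautiously.

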## Methods and Analysis

### Study Design

Double-blinded randomized controlled trial (RCT). Phase I, known medicine (memantine) tested for new indication (treatment of negative symptoms in psychosis).

